### Baseline and follow-up measurements

Given the multiple etiologies in patients with FI, no test should be expected to yield consistent results in all patients with FI. Therefore, no standard protocol is available for the assessment and diagnosis of FI. The chosen tests at baseline (except for the questionnaires) are recommended by the American Gastroenterological Association, being procedures of value (symptom diary, physical examination, anal endosonography, anorectal manometry, rectal and anal sensory testing) and being procedures of possible value (defecography) [29]. As these diagnostic tests are part of the standard diagnostic assessment in the University Hospital Maastricht, participation in the trial will not burden the patient additionally. The following baseline measurements are done during the first and second patient visit:

▪ Vaizey incontinence score: this score reflects the severity of FI and ranges from 0 (complete continence) to 24 (complete incontinence) (Table 1) [28]. The Vaizey score is a widely used severity score and it is reported to be a reproducible score, which correlates highly with physicians' clinical impression [28]. Recently, it has also been demonstrated that higher Vaizey scores are associated with more reported problems in general health domains [30] and that changes in Vaizey score reflect patients' subjective perception of relief [31].

**Table 1 T1:** Fecal incontinence score according to Vaizey et al. [28]

Incontinent	Never	Rarely	Sometimes	Weekly	Daily
Solid stool	0	1	2	3	4
Liquid stool	0	1	2	3	4
Gas	0	1	2	3	4
Alteration in lifestyle	0	1	2	3	4
					
				No	Yes
Need to wear a pad or plug				0	2
Taking constipating medication				0	2
Lack of ability to infer defecation for 15 minutes				0	4

Minimum score = 0 = perfect continence; maximum score = 24 = totally incontinent Never: no episodes in the past 4 weeks; rarely: one episode in the past 4 weeks; sometimes: > 1 episode in the past 4 weeks, but < once a week; weekly: one or more episodes a week but < one a day; daily: one or more episodes a day

▪ Medical history: the medical history assesses gender, age, duration of complaints, risk factors (surgical, obstetric, neurological, metabolic) and medication use.

▪ Physical examination: digital rectal examination is used to assess anal pressure at rest and pressure during contraction. Sphincter defects can be located and palpated, especially during contraction. In women, the presence of a rectocele can be established.

▪ Anorectal manometry: anorectal manometry is performed to measure anal sphincter pressures. The test is performed in the left lateral position and flexed hips to 90 degrees. Anal manometry takes place according to the water-perfused technique. The single use manometric catheter (Medtronic Inc., Skovlunde, Denmark) is introduced, which is connected to a computer-assisted polygraph (Polygraf™ ID, Medtronic Inc., Skovlunde, Denmark) and stabilized in the anal sphincter complex. After positioning the catheter in the maximal pressure area, the basal sphincter pressure, maximum squeeze pressure and rectal anal inhibitory reflex are measured.

▪ Rectal capacity measurement: the measurement is performed by introducing a single use manometric catheter (Medtronic Inc., Skovlunde, Denmark) in the rectum, which is connected to a computer-assisted polygraph (Polygraf™ ID, Medtronic Inc., Skovlunde, Denmark). The catheter is inflated with air with slow increments. The volumes are recorded at which first sensation is noticed (sensory threshold), an urge to evacuate is produced (urge sensation), and volume at which pain becomes intolerable (maximum tolerated volume).

▪ Anorectal sensation: a St. Mark's glove pudendus electrode is placed on the index finger and introduced into the anal canal. An increasing electrical current (mAmp) is gradually applied until the threshold of sensation is reached. Anorectal sensation is measured at two places: three o'clock and nine o'clock in the transversal plane.

▪ Anal endosonography: anal endosonography provides an anatomical image of the anal sphincters and pelvic floor. This technique gives an instant excellent image of the condition of the sphincters and establishes the size of a possible internal or external anal sphincter defect. Anal endosonography is performed with an ultrasound scanner with radial endoscopic probe and a 7.5-MHz transducer. The probe is covered with a lubricant and a condom. After application of a final lubricant the probe is introduced in the anal canal with the patient in the left lateral or prone position. The probe is slightly withdrawn, so all the different levels of the anal sphincter complex can be visualized.

▪ Defecography: defecography is a dynamic radiological study of attempted defecation and shows both the functional aspects of defecation and defects in anorectal anatomy. Patients are instructed to drink contrast medium diluted water before examination. The test starts with the patient in left decubital position. Through an injection pistol barium paste is manually injected in the rectum. In female patients gel is also injected via a syringe in the vagina. The perineum is located with a gel solution as well. Subsequently, the entire x-ray table is tilted upright 90° and the patient is seated on a specially developed radiolucent defecography chair. After the test the patient is instructed to drink sufficiently to eliminate the contrast.

▪ Diary: the diary gives insight into the defecation pattern, involuntary incontinence episodes, pad use, presence of urge feelings, presence of urinary incontinence, alteration in daily activities, ability to infer defecation and medication use of a patient. The diary monitors three weeks. Since FI often goes together with urinary incontinence, additional questions will be included concerning the severity of urinary incontinence. Since limited information is available about the quantity of absorbent material use and the associated costs, the diary will enclose additional questions to get more insights into this domain and estimate accompanying health care costs.

▪ Fecal incontinence quality of life scale (FIQL): the FIQL is a disease-specific quality of life scale, comprising four scales: lifestyle (10 items), coping/behavior (9 items), depression/self-perception (7 items), and embarrassment (3 items). The FIQL has shown to be reliable and valid [32]. A separate quality of life scale is included as FI is considered to highly influence patients' daily life since uncertainty exist on when incontinence episodes may occur.

▪ PREFAB-score: the PREFAB-score is a modified version of the widely used and accepted PRAFAB-score in the urinary incontinence field. The PRAFAB-score is a simple and quickly obtained score which summarizes several objective and subjective components of the severity of urinary incontinence complaints (ranging from 5–20) [33]. The score has proven to be reliable, valid and responsive [34]. Since most of the PRAFAB-score, except for the "amount" item, is applicable to fecally incontinent patients as well, it is suggested to adapt the PRAFAB-score to fecally incontinent patients. From the patients' point of view, two aspects about excretion of feces are reported to be highly embarrassing and affecting social life and body image: whether the excretion can be held up by a pad or not and whether excretion can be smelled by the environment or not. These two aspects, reflecting social limitations, are therefore integrated in the modified PRAFAB-score (min-max = 6–20; range = 15).

▪ Global perceived effect (GPE) (Table 2): this subjective score reflects the change in complaints after physiotherapy treatment compared to the period before treatment and ranges from 1–9 points. A score of 8 or 9 indicates much worsening of complaints and is an indication to consider co-interventions.

**Table 2 T2:** Global perceived effect (GPE-score)

To which degree have your complaints changed compared to the period before physiotherapy treatment?
At the moment, the complaints are .....
1. Very much improved
2. Much improved
3. Moderately improved
4. Slightly improved
5. Unchanged
6. Slightly worse
7. Moderately worse
8. Much worse
9. Very much worse
..... compared to the period before physiotherapy treatment

Follow-up measurements are scheduled at 3, 6 and 12 months after inclusion. Primary outcome measure is the Vaizey score [28]. Success after physiotherapy is defined as a reduction in Vaizey score of more than four points (16.7%) compared to baseline measurement. Recently, it is reported that patients who rated their situation to be better, improved four points on the Vaizey score [31]. Secondary outcome measures are anorectal resting and squeeze pressure, rectal capacity, anorectal sensation, diary results, FIQL, PREFAB-score and GPE-score.

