**Figure 1 F1:**
[figure not shown]
**Flowchart of the PhysioFIT-study**. t = point in time; VS = Vaizey score; MH = medical history; M = medication use ; PE = physical examination; DI = diary; AM = anorectal manometry; RC = rectal capacity measurement; AS = anorectal sensation; AE = anal endosonography; D = defecography; FIQL = fecal incontinence quality of life scale; PREFAB = modified PRAFAB-score; GPE = Global Perceived Effect-score; PFMT = pelvic floor muscle training; RBT = rectal balloon training; VS (-) = reduction on VS < 4 points; VS (+) = reduction on VS ≥ 4 points; GPE (+) = score 1–7 on GPE scale; GPE (-) = score 8 or 9 on GPE scale

It is hypothesized that patients receiving the combined training will have a larger reduction on the primary outcome measure.

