### Sample size

The sample size is calculated based on data from a recently published cohort study on pelvic floor rehabilitation in fecally incontinent patients [31]. Patients who reported their situation to be better after pelvic floor rehabilitation showed a mean improvement score of 4.33 points on the Vaizey score and patients who rated their situation to be equal or (much) worse showed a mean improvement score of one point (baseline average Vaizey score is 18). As subjective improvement can not be projected as decimals on the Vaizey score, we calculated two sample sizes: (1) with exact scores and (2) with absolute scores to correspond with the Vaizey score and estimate of the minimally important change (MIC). The absolute difference in improvement of four points between the patients who rated themselves to be better and the patients who rated themselves to be equal or (much) worse is considered the MIC on the Vaizey score between both trial arms [31].

The first sample size is calculated using an average Vaizey score of 13.67 and a standard deviation of 8.45 for sample 1 and an average Vaizey score of 17 and a standard deviation of 3.90 for sample 2, which resulted in a sample size of 106 patients. The second sample size is calculated using an average Vaizey score of 13 and a standard deviation of 8.45 for sample 1 and an average Vaizey score of 17 and a standard deviation of 3.90 for sample 2, which resulted in a sample size of 73 patients. The sample size is in a range of 73 to 106 patients and we decided to include at least 106 patients to feel confident about the required sample size.

All calculations assume a one-sided effect (first trial arm has a better outcome than second trial arm), an alpha of 0.05, a power of 80% and an expected drop-out of 10%. It is expected that the drop-out will be minimal since patients will be greatly motivated to participate and adhere to the protocol, by experiencing such an embarrassing and socially restricting disorder.

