### Co-interventions

After three months follow-up the physician evaluates the Vaizey score and the GPE-score. In case of an improvement of less than four points on the Vaizey score and/or a GPE-score of eight or nine, the clinician decides upon further therapeutic steps. If necessary, co-interventions are allowed after three months follow-up, although this should be avoided as much as possible. Examples of co-interventions are sacral nerve stimulation, anal repair or lavage. During physiotherapy treatment, patients are not allowed to use anal tampons.

The most common used drugs in patients with moderate to severe FI are Loperamid and sometimes Norit. Medical interventions and/or diet changes are first tried in the conservative management of patients with FI. If patients do not benefit from medical interventions, usual care implies referral for physiotherapy interventions. So, the majority of patients do not use drugs before physiotherapy management since they appeared not to be helpful. Nevertheless, patients who use drugs before starting with physiotherapy interventions are instructed to follow an unchanged stable medical regimen. Therefore, ongoing and change in medication use are monitored during the trial. In the analysis we will account for co-interventions, such as medication use.

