### Secondary goals

Secondary goals of the PhysioFIT-study are to assess the psychometric properties of the PREFAB-score in clinical practice. In addition, baseline measurements are checked for their ability to predict outcome of physiotherapy.

Furthermore, the responsiveness of the Vaizey score is reviewed. The Vaizey score is a more common used severity score in surgical trials. But less is known about the responsiveness of the Vaizey score in physiotherapy trials. One study with comparable in- and exclusion criteria and study population made a first attempt to correlate the Vaizey score with a Global perceived effect score (31). Patients with a decrease of 9 points rated their situation "much better" than before physiotherapy treatment, patients with a decrease of 4 points rated their situation "better" and the group that rated their situation "(much) worse or equal" had a decrease in 1 point (patients were asked in a standardized interview to score their current situation on a scale of 1 (much worse), 2 (worse), 3 (no change), 4 (better), or 5 (much better)). We decided that rating the patients' situation as "better" is a minimally important change (MIC), expressed in an absolute number and not in a certain percentage.

Next to the Vaizey score we included the subjective GPE score (range 1–9) in our trial as an additional outcome measure, as we believe it is important to further investigate the responsiveness of the Vaizey score in patients with FI in physiotherapy trials.

Finally, it is expected that the outcome after physiotherapy interventions is dependent on the baseline Vaizey score; therefore we will perform a stratified analysis on baseline severity scores and change scores.

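### The success cut-off of more than four Vaizey points contradicts its own 16.7% and rationale, the MIC and the Figure 1 split, all of which sit at four points

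*Protocol article*

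**What the plan says.** Only one sentence in the protocol article defines success. In Baseline and follow-up measurements, straight after the primary outcome is named, it reads: "Success after physiotherapy is defined as a reduction in Vaizey score of more than four points (16.7%) compared to baseline measurement". The sentence that follows supports this with an earlier cohort, in which patients who felt better had improved by four points.

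Four other places use the number four:

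- **Figure 1 legend:** "VS (-) = reduction on VS < 4 points" and "VS (+) = reduction on VS ≥ 4 points".
- **Co-interventions:** at three months the clinician decides on further steps "In case of an improvement of less than four points on the Vaizey score and/or a GPE-score of eight or nine".
- **Secondary goals:** in the same cohort, "patients with a decrease of 4 points rated their situation" as better, and the authors adopt that rating as the MIC, expressed as an absolute number of points.
- **Sample size:** a four-point difference in improvement "is considered the MIC on the Vaizey score between both trial arms". This is a difference between groups, not a change within a patient.

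**The concern.** On a whole-number score, more than four and at least four are different rules. The first starts at five points and the second at four. The success sentence uses the first in words and the second in its percentage, and the evidence cited for it is an improvement of four. The Figure 1 legend uses the second.

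A patient who improves by exactly four points has the change that the protocol calls minimally important and falls in the VS (+) group, yet does not count as a success. What is at stake is the success rate reported in each arm, and whether it agrees with the three-month VS (+)/VS (-) split. With the text as it stands, a reader could not tell whether a published success rate counts these patients.

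**Working it through.** **1. The plan's own percentage.** The Vaizey score runs from 0 to 24 (Baseline and follow-up measurements, Table 1).

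- 4/24 = 0.1667 = 16.7%, the stated figure.
- The smallest whole-number change above four is five: 5/24 = 20.8%.
- Taking the percentage against the average baseline of 18 (Sample size) does not rescue the wording: 4/18 = 22.2%.

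So 16.7% belongs to a cut-off of four, not to one above four.

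**2. Can a change of exactly four occur?** Yes. Every item in Table 1 scores whole numbers. The item on holding back defecation for 15 minutes scores 0 or 4, so losing that symptom alone gives a change of four. The pad item and the constipating-medication item score 2 each, and 2 + 2 = 4.

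**3. The patient with a change of exactly four, place by place.**

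| Place | Rule | Result at exactly 4 |
|---|---|---|
| Success definition, words | > 4 | not a success |
| Success definition, percentage | 16.7% = 4/24 | at the stated percentage |
| Figure 1 legend | ≥ 4 is VS (+) | VS (+) |
| Secondary goals | MIC tied to a decrease of 4 | reaches the MIC |
| Co-interventions, Vaizey part | < 4 | not triggered |

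**4. Does the cut-off enter the sample size?** Inputs from Sample size: SDs 8.45 and 3.90, one-sided alpha 0.05, power 80%, drop-out 10%, and means of 13.67 versus 17 (difference 3.33) or 13 versus 17 (difference 4).

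n per arm = (8.45² + 3.90²)(z₀.₉₅ + z₀.₈₀)² / difference², with 8.45² + 3.90² = 71.40 + 15.21 = 86.61 and (1.645 + 0.842)² ≈ 6.18.

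- Difference 3.33: 48.29 per arm, 96.6 in total; × 1.1 = 106.2 (stated: 106).
- Difference 4: 33.47 per arm, 66.9 in total; × 1.1 = 73.6 (stated: 73).

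Both figures are reproduced without a success cut-off, so neither depends on it.

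**5. How many patients would be reclassified? (illustration)** Assume that whole-number changes follow a rounded normal distribution, so the share at exactly four is P(3.5 < X < 4.5). The means are the cohort improvements in Sample size (18 − 13.67 = 4.33 and 18 − 17 = 1). Using the SDs there as SDs of change is my assumption; the article attaches them to average scores.

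| Mean, SD of change | Share at exactly 4 | Of 106 patients | Success, ≥ 4 | Success, > 4 |
|---|---|---|---|---|
| 4.33, 8.45 | 4.7% | 5.0 | 53.9% | 49.2% |
| 1, 3.90 | 7.6% | 8.1 | 26.1% | 18.5% |
| 4, 5 (both assumed) | 8.0% | 8.5 | – | – |
| 4, 4 (both assumed) | 9.9% | 10.5 | – | – |

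If the first two rows stood for the two arms, the difference in success would be 53.9 − 26.1 = 27.8 percentage points with ≥ 4 and 49.2 − 18.5 = 30.7 with > 4: about 3 points apart, in the same direction.

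**The case against.** The strongest reply is that little rests on this cut-off. The primary outcome is the Vaizey score, the hypothesis concerns a larger reduction on it, and the sample size uses means. Data analysis plans analysis of variance on mean change and names no comparison of success proportions, and success is not among the listed secondary outcomes. All of this stands. A reader might infer that the main result or the patient numbers are in doubt; the article does not support that.

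A reader might also infer that the article calls the same patient both a success and a failure. It does not. Only the definition uses the word success. The Figure 1 legend labels groups VS (+) and VS (-), and Co-interventions sets a trigger for a clinical decision, which could legitimately differ from a success threshold. The MIC passages say four points, never four or more; they report group results, and the one in Sample size is a between-arm quantity. These limits narrow the point, but the success sentence still conflicts with its own percentage and rationale, and a MIC of four is reached at four.

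A third inference would be that the analyst is free to choose the rule after seeing the data. That goes too far: there is one explicit definition to follow, and the doubt comes from the percentage and rationale beside it.

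The size is also open to challenge. The two distributions describe cohort patients grouped by their own rating, not randomised arms, and a normal with SD 8.45 fits poorly on a 0 to 24 scale. The counts are illustrative only.

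**Conclusion.** The inconsistency is real and nothing elsewhere in the article resolves it. In words the success threshold is five points or more; its percentage, its rationale, the within-patient MIC and the Figure 1 legend all point to four.

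Only the reported success classification is affected, for about 5% to 8% of patients (roughly 5 to 8 of 106) if changes are rounded normal and the sample-size SDs apply to change. The share is 8% to 10% if the SD of change is assumed to be 4 to 5. The figures show no changed conclusion between the arms. Severity is minor to moderate; it is not a must-fix.

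**What to change.** In Baseline and follow-up measurements, define success as a reduction in Vaizey score of four points or more from baseline (≥ 4, 16.7% of the 24-point scale), and fix this before analysis. That form agrees with the percentage and rationale already given there, with the MIC in Secondary goals and with the Figure 1 legend. Use the same inequality wherever the success endpoint is described.

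The success definition, the Figure 1 legend and Co-interventions should then be read together and reconciled. The co-intervention trigger is a clinical rule and is left to the clinical team.

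The cost is a few words. No sample size, visit or measurement changes.

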### Data analysis

In case of longitudinal missing data, imputation is performed with the last observation carried forward method. Main outcome is tested according to the intention to treat principle. Both treatment groups are checked for comparability regarding baseline data. An independent t-test is done for continuous variables and a Chi-square test for categorical variables. Analyses are performed to compare differences within groups between baseline and short-term follow-up (3 months) and long term follow-up (6 and 12 months) regarding primary and secondary outcome measures. A subgroup analysis is done for the patients with and without co-interventions. Analysis of variance is used to determine the difference in mean change of outcome measure between clinical subgroups. A two-tailed p-value of 0.05 is considered to indicate statistical significance. Data analysis is done using SPSS version 13.0 (SPSS, Inc., Chicago, Illinois). Confounders that are taken into account are presence of urinary incontinence, use of anal tampons, compliance and medication use.

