### Spin off

Often, a trial is designed with the objective to make a difference in clinical daily practice. This section elaborates on what we believe might influence clinical practice.

Based on the results of this trial, baseline measurements are checked for their ability to be a prognostic factor for a good or poor outcome after physiotherapy. In this way, patients can be selected who benefit most of the proposed physiotherapy intervention. Furthermore, this trial can give information on the number of physiotherapy sessions after which more sessions are of no further benefit. Continuation or ending of therapy will have the same outcome at that point. Finally, if the effectiveness of a certain physiotherapy intervention is established, physicians can make a well-founded decision for referral to physiotherapy treatment, in stead of proceeding with surgical treatment. In conclusion, this trial might add to clearer referral patterns and better cooperation between physicians and physiotherapists.

In case of insufficient result of physiotherapy and proceeding to surgical treatment, the received physiotherapy intervention can still be of value. Patients already learned to be aware of their pelvic floor muscles and know how to contract them in an environment without post-surgical stress. Besides, their pelvic floor is probably in a better condition. Future research in this area can focus on the effect of different pre-operative physiotherapy interventions on the success of surgery in FI.

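### No visit is named for the Vaizey primary outcome or the success rule, late Vaizey results can include the effect of rescue treatment, and the with/without co-intervention subgroup does not remove it

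*Protocol article*

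**What the plan says.** Under Baseline and follow-up measurements, the Protocol article schedules visits at 3, 6 and 12 months after inclusion and makes the Vaizey score the primary outcome. It then adds: "Success after physiotherapy is defined as a reduction in Vaizey score of more than four points (16.7%) compared to baseline measurement". No visit is attached to either.

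Under Co-interventions, the physician reviews the Vaizey and global perceived effect (GPE) scores at 3 months. "In case of an improvement of less than four points on the Vaizey score and/or a GPE-score of eight or nine, the clinician decides" on further treatment. Rescue is permitted but discouraged: "If necessary, co-interventions are allowed after three months follow-up, although this should be avoided as much as possible". The article goes on to show what kind of treatment is meant: "Examples of co-interventions are sacral nerve stimulation, anal repair or lavage". The section ends with a general undertaking that the analysis will allow for co-interventions. It gives medication as the only example and names no method.

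Under Data analysis, the main outcome is tested by intention to treat, and the comparisons cover "differences within groups between baseline and short-term follow-up (3 months) and long term follow-up (6 and 12 months) regarding primary and secondary outcome measures". The one concrete step on co-interventions is: "A subgroup analysis is done for the patients with and without co-interventions". The confounders listed there include medication and anal tampons but not surgery, neuromodulation or lavage.

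Under Spin off, "baseline measurements are checked for their ability to be a prognostic factor for a good or poor outcome after physiotherapy". If effectiveness is shown, "physicians can make a well-founded decision for referral to physiotherapy treatment, in stead of proceeding with surgical treatment".

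**The concern.** The visits after 3 months follow a decision point at which patients who did poorly may move to a different and possibly more effective treatment. A Vaizey change from baseline to 6 or 12 months then mixes physiotherapy with rescue. If the success rule is applied at those visits, a patient who failed physiotherapy and improved after anal repair counts as a physiotherapy success.

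The article wants its results to inform the choice between physiotherapy and surgery, and to identify who does well on physiotherapy. Crediting surgery to physiotherapy would mislead both uses. If rectal balloon training (RBT) works, more patients on PFMT alone are likely to meet the rescue trigger, and any late contrast between the arms would be pulled toward zero.

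The stated remedy is itself a problem. Membership of the subgroup without co-interventions depends on the patient's own 3-month result. Dropping rescued patients removes failures from the denominator and no longer compares the groups as randomised.

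**Working it through.** **1. Which visit is intended.** Two sessions a week for 3 weeks is 6 sessions, and one a week for 6 more weeks is another 6. That makes 12 sessions in 9 weeks (Physiotherapy intervention). Adding up to 3 weeks from referral to the first session (Referral) gives week 12. The schedule and the 3-month review both point to 3 months, but the visible text does not say so.

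**2. The plan's own figure.** With n per arm = (8.45² + 3.90²)(1.645 + 0.842)²/3.33² = 48.29, the total is 2 × 48.29 × 1.1 = 106.2, against the stated 106. With a difference of 4, n per arm is 33.47 and the total is 73.6, against the stated 73. The sample size reproduces and is not affected by this point.

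**3. Who could meet the Vaizey trigger.** Assume normal changes with means 4.33 and 1, and use the planning SDs 8.45 and 3.90 as SDs of change.
- Combined arm: P(change < 4) = Φ((4 − 4.33)/8.45) = 48%.
- PFMT alone: P(change < 4) = Φ((4 − 1)/3.90) = 78%.

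If the planned effect is real, eligibility for rescue differs by arm. Eligibility is not uptake, and the article gives no uptake figure.

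**4. Within-arm illustration.** Take 106/2 = 53 per arm and assume 20 successes at 3 months: 20/53 = 37.7%. Of r rescued patients, all assumed non-successes at 3 months, s later pass the rule. Everyone else is assumed unchanged. The mean shift is r × g/53, where g is an assumed gain of 4 to 9 points. Those two values are the changes that Secondary goals reports for patients rating themselves better and much better after physiotherapy; they are not surgical data.

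| r, s | As counted, (20+s)/53 | Subgroup without rescue, 20/(53−r) | Rescue as non-success | Mean shift, points |
|---|---|---|---|---|
| 2, 1 | 39.6% | 39.2% | 37.7% | 0.15–0.34 |
| 5, 3 | 43.4% | 41.7% | 37.7% | 0.38–0.85 |
| 10, 6 | 49.1% | 46.5% | 37.7% | 0.75–1.70 |

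**5. Between arms.** Each extra rescued patient on PFMT alone narrows the mean difference by 4/53 to 9/53, or 0.08 to 0.17 points. Three extra narrow it by 0.23 to 0.51, so 3.33 becomes 3.10 to 2.82. Each extra rescue success narrows the success gap by 1/53 = 1.9 percentage points. With equal rescue in both arms, this dilution of the mean difference is absent.

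**6. The subgroup without co-interventions.** Use the model in step 3 and assume that half of those below the trigger are rescued.
- The subgroup keeps 76% of the combined arm and 61% of PFMT alone.
- Success in it is 68% against 36%, instead of 52% against 22% in the full arms.
- The mean difference becomes 4.6 instead of 3.33.
- With an SD of 5 in both arms, the mean difference stays at 3.34, but success still rises from 53% to 69% and from 27% to 43%.

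Selection raises success within each arm in both settings. Its effect on the between-arm difference depends on the unknown spread.

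**The case against.** The strongest reply is that the visible text already favours 3 months and that no success proportion is a stated analysis. The primary outcome is the Vaizey score, and Data analysis speaks of within-group differences and mean change. This largely stands. A reader might infer that the plan intends to report late success rates with rescue credited to physiotherapy, but the article schedules no such analysis. The percentages above apply only if the rule is read late. The late within-arm Vaizey change, however, is a stated analysis and carries the same mixture.

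Figure 1 is not shown. Its legend defines a Vaizey split at four points and may place it at a visit, so the absence of a visit can be asserted only for the text available.

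It would be wrong to say that the plan ignores co-interventions, since it undertakes to allow for them, and the detail could sit in a fuller document. But that sentence names no method and only medication, while the one concrete method that is stated is the outcome-selected subgroup.

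Late intention-to-treat results that include permitted later care answer a legitimate question. That stands, and the fix keeps them. They simply do not describe physiotherapy alone.

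The magnitudes rest on assumed counts, and rescue is discouraged. That stands too. The rise in the subgroup follows directly from assuming that every rescued patient was a failure; the GPE trigger allows exceptions.

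**Conclusion.** The point holds as a minor to moderate one. The text available fixes no visit for the primary outcome or for success, late Vaizey results can include rescue, and the with/without subgroup is a poor remedy because it conditions on a post-randomisation event triggered by the outcome. The size cannot be derived from the article and may be small. The illustrations assume the success count, the number rescued, their gains, and no other change after 3 months.

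Two stronger conclusions are not supported. The 3-month comparison is not compromised, because co-interventions are allowed only after that follow-up. Nor does crediting rescue create a false case for RBT: if more patients on PFMT alone are rescued, a late contrast is diluted, and if the arms do not differ and rescue is equal, that bias is absent. The overstatement of late within-arm results does not depend on whether RBT works.

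**What to change.** - Set the success rule, the main RBT comparison and the prognostic analysis at the 3-month Vaizey score, taken before any co-intervention.
- Keep the 6- and 12-month intention-to-treat results, described as the effect of initial physiotherapy plus later care.
- Report co-interventions by arm.
- Add a supporting long-term analysis that counts surgical, neuromodulation or lavage rescue as non-success in the randomised arm. A medication change alone would not count. This replaces reliance on the with/without subgroup, which can stay as description only.

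The cost is a few words in the success definition and two or three sentences under Data analysis, with no extra patients, visits or data and no change in who may be rescued.

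There are three downsides. Long-term success in the supporting analysis will look less favourable. That endpoint contains a discretionary treatment decision in a trial where patients know their allocation. Some late starters may also not have finished at the 3-month visit: visits run from inclusion, the first session may come up to 3 weeks after referral, and sessions may run for 3 months from then, so treatment can extend to about week 16 (3 + 13).
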